#### **Q.5. Power for Specific Aim 5.**

The trial is 84% powered to detect a 50% reduction in PB/PE in pregnant mothers in the vitamin D supplemented (4,400 IU/day) group. We estimate that the incidence of preeclampsia and/or spontaneous preterm labor in the standard dosing group (400 IU/day) will be 10%, resulting in an estimated sample size of 435 subjects per arm at the end of the antenatal period. Our sample size simulations, show that we will have excellent power to detect a 50% reduction in preeclampsia and/or preterm labor in the vitamin D supplemented group which is what we anticipate based on our preliminary data.

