#### IV. Study Overview and Subject Selection

This is a multicenter, randomized, double-blind, controlled clinical trial that compares high-dose vitamin D3 supplementation (4,400 IU/day) vs. usual dose vitamin D3 supplementation (400 IU/day) in pregnancy to prevent asthma in the women's children. The study base will be all pregnant women from each Clinical Center who have a personal history of asthma and/or allergies or a history of asthma and/or allergies in the biologic father of the child (i.e. a "high risk" cohort for asthma and allergies in the child). Eight hundred seventy women (435 in each arm) will be followed through their pregnancy and delivery, and their infants will be followed up to the age of 3 yrs. All infants who are consuming < 1000 ml of formula per day will be offered vitamin D supplementation (400 IU/day) in accordance with the most recent recommendations from the American Academy of Pediatrics. This includes all infants who are breastfed, either partially or exclusively, and all formula-fed infants until they consume at least 1000 ml of formula. The primary outcomes are doctor-diagnosis of asthma and recurrent wheezing at age 3 yrs. Due to dropouts from miscarriages, stillbirths, other pregnancy complications, and loss-to-follow-up, we expect that we will be left with 660 3-yr old children (330 in each arm) for the analyses of the primary outcome (see Specific Aims in Section II above).

Women who come into their Obstetrician's clinics for their first pre-natal visit will be screened on a daily basis by a Study Coordinator and a physician co-investigator will verify eligibility criteria.

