**Q.2. Power for Specific Aim 2.** We expect that there will be 400 women in each arm for this analysis due to the 8% miscarriage rate. We do not expect there to be significant LTF by delivery. Like the analysis plan for Specific Aim 1, we plan to incorporate interim analyses, using a Lan-Demets spending function with O'Brien-Fleming type bounds. For this specific aim, we plan for three looks, which results in stopping boundaries of  $|z|=3.7103$ , 2.5114, and 1.993, for the first, second, and final analysis, respectively. As above, the thresholds will be adjusted if the recruitment varies from the expected targets. As shown in Table 5 below, we will have excellent power to detect an increase of 20-60% in the proportion of mothers with 25(OH)D levels > 75 nmol/L between the intervention and the control group. The power calculations did not explicitly account for the interim analyses, however, the power should still be >0.999 even after distributing the alpha level across multiple looks.

**Table 5. Power to detect a 20-60% absolute increase in the proportion of mother's with 25(OH)D > 75 nmol/L for 800 patients in a multi-site study\***

| Proportion of mothers with 25(OH)D > 75 nmol/L in 400 IU group | Proportion of mothers with 25(OH)D > 75 nmol/L in 4400 IU group |            |            |
|--------------------------------------------------------------------------|---------------------------------------------------------------------------|------------|------------|
|                                                                          | 90%                                                                | 80% | 70% |
| 0.50                                                              | >0.999                                                                    | >0.999     | >0.999     |
| 0.40                                                              | >0.999                                                                    | >0.999     | >0.999     |
| 0.30                                                              | >0.999                                                                    | >0.999     | >0.999     |

\* 8% miscarriage rate

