## VIII. HUMAN SUBJECTS RESEARCH

### Protection of Human Subjects

#### Risks to the Subjects

**Human Subjects Involvement and Characteristics:** For this project, we will be conducting a clinical trial of “high dose” vitamin D supplementation vs. “usual dose” prenatal vitamins in pregnant women for the prevention of asthma and allergies in the women’s offspring at 3 years of age. We propose to randomize 870 pregnant women during their 1st trimester with 435 women to the “high dose” arm and 435 women to the usual care arm, follow them through their pregnancy and delivery, and follow the women and their offspring until the 3rd birthday of the children, with the expectation that we will evaluate at least 660 three year olds. A brief study description and a copy of the consent form will be given to pregnant women receiving their care at 3 Clinical Centers (Boston, St. Louis, and San Diego) at their first prenatal visit. Women interested in the study will be invited to a separate visit for more detailed explanation and providing informed consent. There are several reasons for this separate visit: 1) allow the pregnant women to review the informed consent, and 2) to assure as much as possible the dedication of the women to participation in the study until the 3rd birthday of their child. Pregnant women will be selected on the basis of an age >18 years but <40 years, ability to speak English or Spanish, intention to participate in the trial for the full 4 years, no pre-existing type 1 or type 2 diabetes mellitus, hypertension, parathyroid or uncontrolled thyroid disease, kidney stones, and sarcoidosis. Written informed consent (in English or Spanish, according to individual preferences) will be obtained from each subject by study coordinators at each Clinical Center prior to voluntary participation. Participating women will be followed during the remainder of their pregnancy, and their newborns will be followed after delivery.

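### The 84% power stated for Aim 5 does not follow from its own inputs: 10% versus 5% gives 80–81% with 435 per arm, and 77–78% with the 400 per arm the plan expects at delivery

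*Supplement*

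**What the plan says.** Q.5 (Power for Specific Aim 5) states: "The trial is 84% powered to detect a 50% reduction in PB/PE in pregnant mothers". The control rate is given as follows: "We estimate that the incidence of preeclampsia and/or spontaneous preterm labor in the standard dosing group (400 IU/day) will be 10" per cent. The sample size is described as "resulting in an estimated sample size of 435 subjects per arm at the end of the antenatal period". Q.5 then claims "excellent power to detect a 50% reduction in preeclampsia and/or preterm labor" in the supplemented group and refers to simulations, but reports no significance level, sidedness or simulation settings.

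Other sections bear on these inputs:

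- **Number randomised.** Section VIII: "We propose to randomize 870 pregnant women during their 1st trimester with 435 women to the “high dose” arm and 435 women" to the usual-care arm. Section IV gives the same 435 per arm.
- **Number at delivery.** Q.2 (Aim 2): "We expect that there will be 400 women in each arm for this analysis due to the 8% miscarriage rate". P.2.b gives the matching total of 800, and Q.2 expects no significant other loss by delivery.
- **Test.** P.3 tests every pre-specified hypothesis at two-sided 0.05, including hypotheses stated in one direction. The Aim 5 plan uses logistic regression with fixed center effects.
- **Endpoint.** Aim 5 in Section II, and its analysis plan, cover birth before 37 weeks, preeclampsia, gestational hypertension and/or HELLP syndrome.

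**The concern.** Three things in Q.5 do not fit together.

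1. The stated power is higher than its own rates and sample size produce under the plan's test.
2. The sample size assigned to the end of pregnancy is the number randomised, so the miscarriage loss applied elsewhere in the plan has been left out.
3. The control rate belongs to a differently defined endpoint. Preterm labor is not preterm birth: the adverse event list in Section VII.J has a separate entry for preterm labor that does not end in delivery. Gestational hypertension and HELLP are also absent from the endpoint to which the 10% is attached.

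The aim was added to a trial whose size was already fixed, and the plan gives that fixed size as the reason for combining the outcomes. The power statement is therefore the reader's only guide to how informative Aim 5 can be. An overstated figure invites too firm a reading of a null result.

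**Working it through.** **Inputs.** Control rate p1 = 0.10 and a 50% reduction, so p2 = 0.05 (Q.5). Sample size n = 435 per arm (Q.5). Two-sided α = 0.05, z = 1.96 (P.3). Number per arm at delivery: 870 × 0.92 / 2 = 400.2, i.e. 400 (Q.2, P.2.b).

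**Step 1: try to reproduce 84% with 435 per arm.**

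*Pooled normal formula:* power = Φ[(p1 − p2 − z·SE0)/SE1], with SE0 = √(2 × 0.075 × 0.925 / n) and SE1 = √((0.10 × 0.90 + 0.05 × 0.95)/n).

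- SE0 = 0.01786 and SE1 = 0.01778.
- (0.05 − 1.96 × 0.01786)/0.01778 = 0.843, and Φ(0.843) = 0.801.

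*Arcsine approximation* (the one Q.1 uses for its own cross-check): h = 2(asin√0.10 − asin√0.05) = 0.6435 − 0.4510 = 0.1925, and power = Φ(h√(n/2) − 1.96).

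- 0.1925 × √217.5 = 2.839, and Φ(0.879) = 0.810.

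The stated 84% is not reproduced; the shortfall is 3 to 4 points.

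**Step 2: the same with 400 per arm.**

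- Pooled: Φ(0.728) = 0.767.
- Arcsine: 0.1925 × √200 = 2.722, and Φ(0.762) = 0.777.

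**Step 3: does the choice of method explain the gap?** All rows are two-sided at 0.05.

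| Method | 435 per arm | 400 per arm |
|---|---|---|
| Pooled normal | 80.1% | 76.7% |
| Unpooled normal | 80.3% | 76.9% |
| Arcsine | 81.0% | 77.7% |
| Exact enumeration, Pearson test | 81.1% | 77.6% |
| Exact enumeration, Wald log-odds test | 80.3% | 76.8% |
| Exact enumeration, likelihood ratio test | 81.1% | 77.7% |
| Simulated center-adjusted logistic Wald test (40,000 replicates, three equal sites) | 80.5% | 76.7% (399 per arm) |
| Fisher exact | 77.1% | 73.7% |
| Continuity-corrected | 76.2% | 72.3% |

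No two-sided method reaches 84%. Spreading the control rate over 5–15% across sites (an assumed range) gives 80.8% at 435 per arm, so site heterogeneity does not close the gap.

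**Step 4: work backwards.** The pooled formula returns exactly 435 per arm for 80% power. For 84% it needs 483 per arm, and the arcsine formula needs 472. So 435 per arm corresponds to 80% power.

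**Step 5: what would give about 84%?**

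- *A one-sided test.* At 435 per arm, one-sided 0.05 power is 84.9% with a continuity correction, 85.8% with Fisher's test and 87.7% with the plain pooled formula. At 400 per arm the plain pooled formula gives 85.2%. P.3 excludes one-sided testing.
- *A higher control rate.* With a 50% reduction from 11%, 435 per arm gives 84.0% (pooled). Q.5 states 10%.

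**Step 6: sensitivity to the control rate.** With 400 per arm and a 50% reduction, pooled power is 71.9% at a control rate of 9%, 76.7% at 10%, 80.8% at 11% and 84.4% at 12%. Rates other than 10% are assumptions; the documents give none for the Aim 5 composite.

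**The case against.** The strongest reply has three parts.

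**The 400 per arm is stated for Aim 2, not Aim 5.** The protocol gives no evaluable number for Aim 5 other than 435. Section IV says "Eight hundred seventy women (435 in each arm) will be followed through their pregnancy and delivery", the analysis is by intention to treat, and a woman who loses the pregnancy could already have had preeclampsia or gestational hypertension recorded. This stands to the extent that 400 is carried over by inference. The inference is well supported: the 8% loss applies to all 870 women, Aim 5 is likewise settled by delivery, and Q.5 itself places its number at the end of pregnancy. Keeping all 435 does not recover the stated figure either.

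**The endpoint mismatch may work in the plan's favor.** The Aim 5 composite adds gestational hypertension and HELLP, so its control rate could exceed 10%. At a fixed 50% reduction a higher rate raises power, and one or two percentage points more would restore about 84%. This is a fair point, and it means that 77–78% is not an established power for the composite actually analysed. Nor does it validate 84%: Q.5 computes from 10%, and the protocol gives no rate for the composite.

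**The consequences are limited.** Aim 5 is secondary, was added in March 2011 to a fixed sample, and its power figure drives no enrolment or stopping decision. This is correct. It limits how much rests on the point, but the stated number is still wrong.

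**Conclusion.** The concern holds. On Q.5's own inputs and the two-sided 0.05 test required by P.3, power is 80–81%, so 84% is overstated by 3–4 points even if every randomised woman is evaluable. With the plan's own 8% miscarriage loss it is 77–78%, an overstatement of 6–7 points; the miss rate becomes 22–23% instead of 16%.

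These figures assume a 10% control rate, a 50% reduction, 1:1 allocation and no interim testing of Aim 5; Q.5 describes no interim looks. If the final critical values used for the other aims applied (1.993 or 2.0141), pooled power at 435 per arm would fall further, to about 79% or 78%. Power for the composite as defined in Aim 5 cannot be derived from the documents, because no control rate is given for it. The power for the primary outcome is unaffected.

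**What to change.** In Q.5:

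- Replace 84% with about 77–78% power at 400 evaluable women per arm, and add that it would be 80–81% if all 435 are evaluable.
- State which women form the Aim 5 denominator, and specifically whether those with a miscarriage or stillbirth are included.
- Give the significance level, sidedness and method behind the figure.
- Remove the description of the power as excellent.
- State an expected control rate, with its source, for the composite in Aim 5 (birth before 37 weeks, preeclampsia, gestational hypertension and/or HELLP), and report power for that endpoint over a plausible range of rates.

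The cost is a recalculated figure and a few sentences. No additional participants and no change to the Aim 5 analysis are needed. The price is a less favorable stated power, unless a documented, higher control rate for the composite supports a better one.

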#### **Q.6 Missing data considerations**

It is expected that missing data will be infrequent, that the treatment is sufficiently benign that any missingness would be unrelated to treatment group, and that the outcome ascertainment process is compatible with standard medical care for children. Thus it is reasonable to predict that missing data would be missing “completely at random” (MCAR) and that inference based on the complete cases would be valid, though only slightly inefficient, if missingness is rare (less than 5%) . Methods are available to assess the compatibility of response patterns with the MCAR condition (Chen and Little, 1999), and these will be used to diagnose the missing data situation. If missingness is not rare, and it is desired to improve the

efficiency of the analysis, two possible approaches to handling the imputation are described below.

Approach A: Impute the overall (ignoring treatment assignment) incidence of asthma and recurrent wheeze (or the incidence of the secondary outcome of interest) for children that are lost to follow-up, and analyze the resulting imputed dataset as if complete. This is a crude but very simple approach that is often proposed. Approach B: Use subject-specific modeling to determine an imputation distribution for those who drop out. Specifically, model the risk of asthma and recurrent wheeze (or secondary outcome) among completers as a function of baseline covariates, ignoring treatment assignment. Use the covariates  $z_i$  observed on dropouts to predict  $\text{logit}[\Pr(M_i|Z_i)]$ . The predicted estimate is then perturbed by repeatedly drawing randomly from a distribution whose variance is the sample variance in the group of completers. Both analyses will be conducted to examine the similarity of results to the complete case analysis. If the results are consonant, for simplicity, the complete case analysis will be reported along with any variations in findings from the described imputation strategies.

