## Q. Power and sample size

**Q.1. Power for Specific Aim 1.** The trial is designed to detect a 25% reduction in asthma and recurrent wheeze incidence at 3 years in the vitamin D supplemented (4400 IU) group. Based on the observational results in the Viva Study, we estimate that the incidence of asthma and/or recurrent wheeze in the standard dosing group (400 IU) will be 40-50%. This incidence estimate is based on observations from Project Viva and the URECA Project. **In project Viva, the prevalence of persistent wheeze is 44% and of asthma is 56.2% in children born to families with parental history of asthma (about twice the prevalence in children without family history).** These estimates are similar to those observed in the URECA Project in children who have turned 2 yrs old. The children in that cohort had a family history (mom or dad) of asthma or allergies. **In the URECA cohort, 99 of 194 (51.0%) children who have reached their 2nd birthday, have experienced "wheezing or asthma by age 2."** These observed rates in 2 cohorts give us confidence that we will see similar rates when we recruit the high-risk (for asthma and allergies in the child) pregnancies for this clinical trial. We anticipate an 8% miscarriage rate and 17-18% LTF among remaining subjects over the study period, resulting in an estimated sample size of 660 subjects (330 per arm) at the end of the study period. Each power estimate is based on 10,000 simulations. The simulations incorporate an interim analysis plan using the Lan-Demets spending function described in section VII.M, although the power may be slightly lower than the estimates presented here. For our group sequential design, we plan to use a Lan-Demets spending function with four approximately equally-spaced looks (with respect to the amount of information collected) and O'Brien-Fleming type bounds. The software program LANDEM (<http://www.biostat.wisc.edu/landemets/>) was used to calculate the stopping boundaries, which were  $|z|=4.3329, 2.9631, 2.3590$ , and  $2.0141$  at the first, second, third, and final looks, respectively. As noted in N.2.A.1, Lan-DeMets procedure provides a spending function approach which does not require pre-specification of the frequency or timing of interim looks. Therefore, the thresholds will be adjusted if the recruitment targets vary or if the need for more frequent monitoring arises. The hypothesis tests are conducted with two-sided alternatives (i.e. a two-sided p-value). The power reflects the proportion of replicates where the Wald test statistic from the hypothesis test of  $\beta_1=0$  is less than the stopping boundary specified for the first, second, or third looks, where  $\beta_1$  is the coefficient for Vitamin D supplementation status from the logistic regression model outlined in section N.2.a. The replication is considered a 'success' if the stopping boundary is exceeded at any of the analysis times. In the simulations, the incidence of asthma and/or recurrent wheeze at the first and second interim looks is proportionate to the overall incidence expected at the end of the study period (i.e. at the first look, the incidence is one-third of the specified rate; at the second look, it is two-thirds). We do not expect incidence rates of 40-50% to be achieved until the third year of follow-up; therefore, the simulations reflect the approximate amount of information anticipated at each interim analysis.

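### Both imputation analyses in Q.6 leave out treatment arm, so at the planned 17–18% loss they shrink a true effect by about that fraction

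*Supplement*

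**What the plan says.** Section Q.6 of the current protocol opens with a forecast: "It is expected that missing data will be infrequent". It predicts that missingness will be completely at random (MCAR) and regards complete-case inference as valid, with little loss of efficiency, when missingness is below 5%. If missingness is not rare and more efficiency is wanted, it describes two approaches.

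- **Approach A** is to "Impute the overall (ignoring treatment assignment) incidence of asthma and recurrent wheeze" for children lost to follow-up, and then to "analyze the resulting imputed dataset as if complete".
- **Approach B** models risk "among completers as a function of baseline covariates, ignoring treatment assignment". It continues: "The predicted estimate is then perturbed by repeatedly drawing randomly from a distribution whose variance is the sample variance in the group of completers". No rule for pooling the repeated draws is given.

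Both are compared with the complete-case analysis. If the results agree, the complete-case analysis is reported, with any variations noted. Nothing is said about what happens if they disagree.

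Section Q.1 plans an 8% miscarriage rate and "17-18% LTF among remaining subjects over the study period", leaving 660 children, 330 per arm. The footnote to Table 4 uses 18% and 8%. The Addendum to Analysis Plan (section I.A) adds interval-censored event times but neither mentions nor withdraws Q.6.

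**The concern.** An imputation model that omits the variable whose effect is being estimated sets that effect to zero among the imputed children. Blending a zero effect in the dropouts with the real effect in the completers pulls the estimate toward the null, however benign the dropout mechanism. Approach A also counts each filled-in child as an observed one. Approach B leaves its variance undefined.

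Neither approach uses what is known about a dropout after baseline. Wheeze and asthma are asked about every three months (section VI.M), and a diagnosis at any time in the first three years meets the endpoint (section VI.A.1; Addendum, section I.A). Read literally, a child with a reported diagnosis at 18 months who is then lost would be assigned the pooled incidence under A, or a baseline-only prediction under B.

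At stake is the value of the robustness check. If treatment works, A and B will differ from the complete-case result by construction, so their agreement or disagreement says little about whether the missing data matter.

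**Working it through.** **Inputs.** 870 randomised, 435 per arm (section IV); 8% miscarriage, 17–18% loss, control incidence 40–50%, 25% relative reduction (Q.1); two-sided 0.05 (P.3).

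**1. The plan's own figures.** Evaluable children: 870 × 0.92 × 0.82 = 656, and 870 × 0.92 × 0.83 = 664, against the stated 660. Power at 50% against 37.5% with 330 per arm:

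- SE under the null = √(2 × 0.4375 × 0.5625 / 330) = 0.0386
- SE under the alternative = √[(0.5 × 0.5 + 0.375 × 0.625) / 330] = 0.0383
- power = Φ[(0.125 − 1.96 × 0.0386) / 0.0383] = 0.901

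Table 4 gives 0.906. All nine cells of that table reproduce within 2 percentage points.

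**2. Missing fraction.** 870 × 0.92 is about 800 continuing pregnancies, or 400 per arm. With 330 observed, 70/400 = 17.5% are missing, more than three times the 5% condition.

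**3. Dilution.** Let f be the observed fraction, p₁ and p₂ the arm risks and p̄ their pooled value. The imputed arm risks are f·p₁ + (1 − f)·p̄ and f·p₂ + (1 − f)·p̄, so the difference becomes f·(p₁ − p₂).

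- Control: 0.825 × 0.5 + 0.175 × 0.4375 = 0.489
- Treated: 0.825 × 0.375 + 0.175 × 0.4375 = 0.386
- Difference: 12.5 points becomes 10.3
- Odds ratio: 0.60 becomes (0.386/0.614) / (0.489/0.511) = 0.66
- At 40% against 30%: 10.0 points becomes 8.25, and the odds ratio 0.64 becomes 0.69
- At only 5% missing: 0.95 × 12.5 = 11.9 points

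A baseline covariate does not rescue B. A simulation of 1,500 trials with a logistic imputation model, one covariate and perturbed logits gave an odds ratio of 0.658 against a true 0.60.

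**4. Precision, coverage and power.** Simulation of 20,000 trials: 400 per arm, 330 observed, MCAR, 50% against 37.5%, one final test at 1.96. Q.6 does not say how A's fill-in is done, so two readings are shown.

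| Analysis | Mean difference | Mean SE | SD of estimate | Coverage | Power |
|---|---|---|---|---|---|
| Complete case | 0.1246 | 0.0383 | 0.0383 | 94.8% | 0.902 |
| A, incidence filled in | 0.1028 | 0.0348 | 0.0316 | 92.6% | 0.857 |
| A, one random draw | 0.1026 | 0.0348 | 0.0351 | 90.1% | 0.831 |
| B, Rubin's rules | 0.1028 | 0.0379 | 0.0318 | 94.7% | 0.813 |
| B, within-imputation variance only | 0.1028 | 0.0348 | 0.0318 | 92.4% | 0.857 |
| Imputation with arm, Rubin's rules | 0.1245 | 0.0384 | 0.0384 | 95.0% | 0.897 |

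A's SE is 0.0348/0.0383 = 0.91 of the complete-case SE, about 9% smaller. It is not materially below the spread of A's own estimates, so the undercoverage comes mainly from the shifted estimate.

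With no treatment effect (50% in both arms), rejection rates are 3.3% or 5.2% for A and 2.0% for B with Rubin's rules. False positives are not materially inflated.

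**The case against.** The strongest reply is that A and B are sensitivity analyses. Complete cases are reported when results agree, along with any variations, and under MCAR that estimate is well calibrated (coverage 94.8%). Q.6 also commits to an MCAR diagnostic, section P.2 to a check for differential loss by arm, and the Addendum to interval-censored analysis, which can use follow-up before dropout. Giving all dropouts a common risk is moreover a conservative test in a superiority trial, and a benefit that survives it is informative.

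Much of this stands, and it rules out several stronger readings that a reader might infer:

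- **That the reported primary estimate is diluted.** It is not; the dilution is confined to A and B.
- **That both approaches give intervals that are too narrow.** B draws repeatedly. With Rubin's rules its SE is 0.0379 and its coverage 94.7%. Its intervals are too narrow only if between-imputation variance is left out, which the plan does not say. B's fault is the missing pooling rule.
- **That the plan assumes under 5% missing.** The 5% is a condition, and the following text provides for its failure. The contradiction is between the word infrequent and the planned loss.
- **That these are the only missing-data checks, or that quarterly reports go unused throughout the plan.** The diagnostic, the differential-loss check and the Addendum show otherwise. The complaint about unused reports applies to A and B only.

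What the reply does not answer is that Q.6 introduces imputation to gain efficiency, not as a deliberately conservative test. As specified, it loses power and moves the estimate even when its own assumptions hold.

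**Conclusion.** The concern holds in this limited form. Both imputation analyses omit arm and, at the planned loss, shrink a true effect by about 17–18%. Power falls by about 4 to 7 points under A (0.902 to 0.857 or 0.831) and by about 9 points under B with Rubin's rules (to 0.813). A's coverage is about 90–93%, depending on the fill-in. B has no stated pooling rule. The complete-case result is unaffected, but the comparison meant to support it is hard to interpret, and no reporting rule covers disagreement. Separately, the forecast of infrequent missing data conflicts with Q.1 and Table 4.

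The figures assume MCAR, equal loss in both arms, imputation of children lost after a continuing pregnancy, and B read as multiple imputation. If all 435 per arm were imputed, the observed fraction would be 330/435 = 0.76 and 12.5 points would become 9.5.

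**What to change.** - Drop Approach A.
- Replace Approach B with multiple imputation that includes treatment arm, centre, race/ethnicity, baseline parental asthma and atopy, and every quarterly wheeze, asthma and medication report made before dropout. Pool by Rubin's rules.
- Replace the expectation of infrequent missing data with the planned 17–18% loss.
- Report complete-case and imputed results side by side whether or not they agree.

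Putting arm in the model removes the dilution but gives no power of its own (0.897 against 0.902). Any gain in efficiency would have to come from the reports made before dropout; its size cannot be worked out from the documents. A delta-adjusted analysis by arm would be a useful optional addition, because no analysis for data missing not at random is planned.

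The cost is a little more analysis work and no new data.
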